#### Exploratory Analyses

A Pearson correlation coefficient will be used for univariate analysis. Change in self-efficacy will be correlated with psychological and physiological measures. The variables that are found to be the most significant will be entered into a linear regression model to determine what accounts for the variance in self-efficacy. Given the relatively small number of subjects, a maximum of 4 variables will be included in the regression analysis.

Analyses will also be conducted to explore the possible presence of a moderator; emotional self-regulation. A hierarchical multiple regression equation using SAS will be used to test for potential moderating effects.

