**Figure 1 F1:**
[figure not shown]
**'Theoretical Model of Hypotheses to be Tested'**.

**H**_**o **_**2**: At conclusion of the intervention (6 months) and 12 month follow-ups, in comparison to the control group, the MI Group will report higher levels of healthy behaviors (i.e., increased activity as measured by the Weight Loss Behavior Scale [32] and the Dutch Eating Behavior Questionnaire [33]).

**H**_**o **_**3**: At conclusion of the intervention (6 months) and 12 month follow-ups, in comparison to the control group, the MI group will demonstrate increased improvement in psychological functioning as measured by the Peds Quality of Life questionnaire [34], the Child Depression Inventory [35] and the Rosenberg Self-Esteem Scale [36].

**H**_**o **_**4**: At conclusion of the intervention (6 months) and 12 month follow-ups, in comparison to the control group, the MI group will demonstrate improved physiological functioning/decreased metabolic risk as indicated by changes in BMI, body composition, improved lipid profile, insulin resistance, blood pressure and fitness;

**H**_**o **_**5**: Improvements in behavior change and self-efficacy will correlate with reduction in BMI and improved metabolic status.

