#### Sample Size and Outcomes (Table 2)

The primary outcome for this study will be the total self-efficacy score as measured in the Child Dietary Self-Efficacy Scale (CDSS) [30]. Previous studies [38] have shown that the mean CDSS total self-efficacy score at in this population (without any intervention) varies between 5.0 and 6.5 with a standard deviation between 0.5 and 1.4. Previous behaviour studies in this population have shown treatment change in CDSS total self-efficacy scores between 1.1 and 1.9. Based on these preliminary data, assuming no differences between groups at baseline and a standard deviation of 1.0 (no differences between groups) we estimates that a sample size of 16 patients per group would allow the detection of between-group differences of 1.5 units with a standard deviation of 1.0 at an alpha level of 0.05 and 80% power. This estimate needs to be inflated to 20 patients per group in order to account for a 20% attrition rate.

**Table 2 T2:** Analysis of Power

	EF = 1.25	EF = 1.5	EF = 1.75
Power			
80%	22	16	10
85%	26	18	12
90%	28	20	14

With this sample size we would be able to detect a difference of 1.4% in BMI percentile between groups over time assuming a 1.5% standard deviation, a difference of 2.85 points in self-esteem as measured in the Rosenberg scale (assuming a 3.15 points standard deviation and a difference of 6.5 points in the CDI depression scale (assuming a 7.1 points standard deviation). In linear regression models using maximum likelihood algorithm for parameter estimation (4 variables per observation in treatment group), this sample size would allow adjusting for 3 independent variables in addition to treatment group.

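### The exploratory regression chooses its predictors by significance and refits them in the same small sample, so its R-squared is inflated and its p-values are invalid; H5 is only partly covered

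*Protocol article*

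**What the plan says.** The Exploratory Analyses section of the protocol article sets out a two-step procedure. The first step is univariate, by Pearson coefficient: "Change in self-efficacy will be correlated with psychological and physiological measures". The second step is multivariable: "The variables that are found to be the most significant will be entered into a linear regression model", and its purpose is "to determine what accounts for the variance in self-efficacy". The one limit is that "a maximum of 4 variables will be included in the regression analysis", which the article justifies by the small sample. It describes no correction for the selection.

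Two other places bear on this:

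- The Sample Size and Outcomes section, speaking of linear regression models, says that "this sample size would allow adjusting for 3 independent variables in addition to treatment group". That makes four terms, the same number as the cap. The Exploratory Analyses section itself does not name treatment group.
- H5, under Primary Hypotheses, states: "Improvements in behavior change and self-efficacy will correlate with reduction in BMI and improved metabolic status".

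**The concern.** The cap of four limits the size of the final model but not the search that fills it. If the four strongest of many correlates are picked and then judged by ordinary F-tests, t-tests and R-squared in the same patients, those statistics behave as if nobody had searched. A model built from noise can then look as if it explains a quarter or a third of the variance.

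Two related weaknesses go with it:

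- **Treatment group.** The screening correlations are plain univariate ones over both arms. If MI moves two outcomes independently, they will correlate in the pooled sample with no link inside either arm. Selection by significance also does not guarantee that treatment group stays in the regression.
- **H5.** The hypothesis has two halves, self-efficacy and behaviour change, each to be related to BMI and metabolic status. The described correlations start only from self-efficacy.

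At stake is the correlational part of the trial's message. The Discussion makes wider clinical use depend partly on the effects of MI correlating with psychological and physiological improvement.

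**Working it through.** **Inputs from the article**

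- Evaluable patients: the Sample Size section says "a sample size of 16 patients per group would allow the detection of between-group differences of 1.5 units" (power 80%, alpha 0.05, SD 1.0). Sixteen per group gives 2 × 16 = 32.
- Attrition 20%: 16/(1 − 0.20) = 20 per group, which reproduces the enrolment figure (40 in total).
- Model size: at most 4 variables, so 32/4 = 8 patients per variable.
- Detectable BMI-percentile difference 1.4 with SD 1.5: 1.4/1.5 = 0.93 SD. CDSS difference 1.5 with SD 1.0: 1.5 SD.

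The 16 per group does not itself follow from its stated inputs. The normal approximation gives 2 × (1.960 + 0.842)² × 1.0²/1.5² = 6.98, so 7 per group, and the t-test gives 9. That is a separate matter. Here 16 per group serves only as the planned evaluable number.

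**Assumption: number of candidates (K).** The article does not state it. Table 1 lists nine questionnaires besides the two self-efficacy scales and the demographics form. The Procedures section and Appendix add body fat, BMI, waist, glucose, insulin, three lipids, two liver enzymes, three adipokine or inflammatory markers, insulin sensitivity, two blood pressures and fitness. I take K = 10 to 25.

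**Step 1: reference case.** For four pre-specified predictors with no true association, expected R-squared = 4/(n − 1) = 4/31 = 0.13, and the overall F-test rejects in 5% of trials.

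**Step 2: selection.** I simulated an outcome and K candidates as pure noise with n = 32, entered the four with the largest absolute correlation, and fitted ordinary least squares to the same data (10,000 runs per row; repeat simulations differ by a point or two).

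| K | Correlation between candidates | F-test below 0.05 | Mean R-squared |
|---|---|---|---|
| 4 (no selection) | 0 | 5% | 0.13 |
| 10 | 0.3 | 20% | 0.21 |
| 10 | 0 | 28% | 0.24 |
| 15 | 0.3 | 31% | 0.25 |
| 15 | 0 | 47% | 0.29 |
| 20 | 0.3 | 39% | 0.27 |
| 20 | 0 | 62% | 0.32 |
| 25 | 0.3 | 47% | 0.29 |
| 25 | 0 | 73% | 0.35 |

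Forcing treatment group in and selecting the top three does not cure this: over the same range of K, the F-test rejects in about 21% to 65% of runs, with mean R-squared 0.22 to 0.33.

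**Step 3: pooled correlation from treatment effects alone.** With equal arms, no within-arm association and effects d₁ and d₂ in SD units, the pooled correlation is

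r = (d₁d₂/4) / √[(1 + d₁²/4)(1 + d₂²/4)].

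With d₁ = 1.5 (CDSS), 1 + d₁²/4 = 1.5625:

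- d₂ = 0.3: 0.1125/√(1.5625 × 1.0225) = 0.09
- d₂ = 0.5: 0.1875/√(1.5625 × 1.0625) = 0.15
- d₂ = 0.93: 0.35/√(1.5625 × 1.2178) = 0.25

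Simulating 40,000 trials of 32 patients gives mean r of 0.09, 0.15 and 0.26, nominally significant in about 8%, 13% and 30% of trials.

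**Step 4: H5 against the described analyses.**

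| Part of H5 | Described analysis |
|---|---|
| Self-efficacy with BMI and metabolic status | Pearson step, under Exploratory Analyses |
| Behaviour change with BMI and metabolic status | None described |

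**The case against.** The strongest defence is the label. The section is headed exploratory, admits the small sample and caps the model. The primary outcome is the CDSS score compared between groups, and nothing here touches that comparison. This stands, and it limits the severity. It does not make the reported R-squared or p-values right, because the article fixes the selection rule and says that the model will show what accounts for the variance.

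Three stronger readings are tempting, and the article does not support them.

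- A reader might infer that the regression has no treatment term. The Sample Size section provides for treatment group plus three variables. What remains is that the Exploratory Analyses section does not name it and that entry by significance need not keep it.
- A reader might infer that H5 goes untested, or that the regression runs backwards because self-efficacy is its dependent variable. H5 is a correlation hypothesis, correlation has no direction, and the Pearson step covers its self-efficacy half. The regression is never offered as the test of H5. The gap is the behaviour-change half.
- A reader might infer that H5 is a claim about mechanism. It asserts correlation only, not mediation.

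The magnitudes can also be challenged. K is assumed. Four is a maximum, so the R-squared values apply when all four places are filled. The 0.93 SD effect on BMI is a detectable difference, not an expected one, so smaller effects are shown beside it. The 32 is inferred: 40 are to be enrolled, and patients may decline the medical testing, so the number with physiological data may be lower. None of this changes the direction of the bias.

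**Conclusion.** The concern holds as a minor point. Selecting the strongest correlates and refitting them in the same patients overstates fit and invalidates the p-values. Under the assumptions of 32 evaluable patients and 10 to 25 candidates that are uncorrelated or correlated at 0.3, noise alone gives a nominally significant model in about 20% to 73% of trials instead of 5%, and mean R-squared of 0.21 to 0.35 instead of 0.13. It would be too strong to say that noise usually yields a significant model: that is so only for 20 or more uncorrelated candidates.

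The lack of arm adjustment in the correlations matters little if the BMI effect is small (about 8% false positives at 0.3 SD) and more if it is large (about 30% at 0.93 SD), with a 1.5 SD CDSS effect assumed throughout. H5 is listed as primary, but only its self-efficacy half has a described analysis, and that analysis sits under the exploratory heading.

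**What to change.** 1. Replace selection by significance with a small set of predictors named in advance. Treatment group is always included, and the total stays within the cap of four.
2. For H5, state the correlations to be reported: change in self-efficacy and change in behaviour scores, each with change in BMI and with named metabolic measures. Report them as partial correlations adjusted for treatment group.
3. If a data-driven search is kept, label it hypothesis-generating, report no p-values, and give an R-squared corrected for optimism by repeating the whole selection, including the correlation screen, in bootstrap samples.

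The cost is wording in the analysis section and the loss of an open-ended search for predictors. No extra data or patients are needed.

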#### Coding the MI

Therapy sessions will be taped and recordings will be coded using the Motivational Interviewing Treatment Integrity Coding System (MITI), version 3.1. A team of coders led by a trainer from the Motivational Interviewing Network of Trainers (MINT) will code the audio tapes. More than one coder will code each tape to ensure reliability of the coding. This will be important to help counter any bias that may have emerged during data interpretation.

## Discussion

Results from this study are hoped to enhance our understanding of the efficacy of MI with children and adolescents who are overweight or obese. If findings suggest that MI effects positive change to the treatment group over and above the control group intervention, and this correlates to improvement in psychological and physiological health, MI may have wider clinical applications. For example, the results of this study may generalize to other overweight and obese children and adolescents. External validity may be limited by participant demographics such as ethnicity, baseline obesity severity or comorbid diagnoses of weight related disorders such as diabetes, such that the results may not generalize to participants with characteristics that were not well represented in the study. Although attempts will be made to recruit participants of all ethnicities and participants will be matched for age and gender, certain types of participants may be underrepresented. Similarly, the results may not generalize beyond adolescents who are willing to volunteer for research or were motivated by the incentive of weight loss offered for participation. Another possible imitation to our study is the exclusion of parents. Future studies could include MI intervention with youth and their parents.

Health-related problems that accompany obesity are of great concern in the obese pediatric and adolescent population. Youth who are overweight have two to four times increased odds of having low scores for psychological health, self-esteem, and physical functioning [39]. Taken together, it is important that researchers develop empirical psychological interventions, grounded in theory, that will extend obesity treatment from support and education to promote sustained behavior change. As such, if significant results are found, Motivational Interviewing may be acknowledged as an effective treatment modality for child and adolescent obesity.

## Appendix

Subjects participating in the MI study will undergo a number of metabolic tests twice marking the start and end of the study. This testing will be carried out at the SickKids Hospital in the clinical investigation unit (CIU) and the exercise laboratory. Medical history will be obtained, including history of diabetes, hyperlipidemia, fatty liver disease, hypertension in participants and first-degree relatives.

A standard, calibrated scale and wall-mounted stadiometer will be used to measure weight and height, and BMI calculated as weight (kg)/height (m)^2^. Obesity is defined as BMI > 95^th^ percentile for age and gender on the Centre for Disease Control growth curves. Waist circumference will be measured in duplicate to the nearest 0.1 cm at the level of the umbilicus using a non-elastic fiberglass measuring tape (Tech-Med model 4414; Moore Medical Corp., New Britain, Conn). Three trails of above measurements will be completed and the mean taken for analyses. Systolic and diastolic blood pressure measurements will be taken using a Dinamapp device. The mean of 3 readings taken 1 minute apart in the right arm in seated position is recorded. Puberty will be assessed using the method of Tanner [40].

Following insertion of an intravenous catheter in the antecubital fossa, a fasting sample of blood is taken for measurement of glucose, insulin, triglyceride, low density lipoprotein (LDL) and high density lipoprotein (HDL) cholesterol, hepatic enzymes (ALT, AST), and highly sensitive C-reactive protein. Subjects are then given a glucose containing drink (75g Glucodex bottle: 1.75 g/kg to a max of 75 kg) and venous blood samples for insulin and glucose are obtained at 0, 30, 60, 90 and 120 minutes to screen for impaired glucose tolerance and type 2 diabetes. Insulin sensitivity (Si) is calculated by the Matsuda Model where; Si = 10 000/[(fasting glucose × fasting insulin) × (mean glucose × mean insulin)]^1/2^ where glucose is measured in mg/dl and insulin in μU/ml. This is well validated against gold-standard measures of insulin sensitivity in adults and in children with (r = 0.67 - 0.78) [41].

Physical activity will be assessed using the Habitual Activity Estimation Scale (HAES). Physical fitness will be measured using a maximal, incremental cycle ergometer (stationary bicycle) test, according to the Godfrey protocol. Similar to previous investigations, increments will be chosen based on the client's sex, height and physical activity level, so that the client terminates the test in 8-10 minutes due to exhaustion. Peak work capacity (VO_2_max) will be determined and compared to established norms. Additional exercise parameters include the degree of oxygen saturation with exercise, peak heart rate, peak ventilation, peak oxygen consumption and respiratory reserve (ratio of peak ventilation to maximum voluntary ventilation) [43,44].
